## 1. INTRODUCTION AND RATIONALE

The worldwide prevalence of obesity has nearly tripled in the past 40 years, totalling up to over 650 million adults in 2016.(1) Obesity is related to the onset of metabolic disorders, such as metabolic syndrome, type 2 diabetes mellitus (T2DM), non-alcoholic fatty liver disease (NAFLD) and cardiovascular disease (CVD). These diseases are associated with a high morbidity and mortality, making T2DM the ninth leading cause of death worldwide.(2) Apart from causing a high burden on a patients wellbeing, this also leads to a global health and socio-economic burden.

The human diet plays an important role in (metabolic) health and can be a major component in the aetiology of obesity, T2DM and NAFLD.(3-5) The western diet, being energy and relatively low in fibres, is seen as a major contributor to the development of these diseases. However, diet composition may affect food digestion and fermentation, which may have either a beneficial or detrimental effect on human metabolism and health.(3) The gut microbiome, consisting of trillions of microbes and being responsible for the fermentation of indigestible food components, is being more and more thoroughly understood, and is recognized for its important role in gut health, mucosal immunity and integrity, and in metabolic and psychological health of its host.(3-6)

The microbiome is able to ferment indigestible food components, such as prebiotics, dietary fibres and resistant starches. Fermentation of these carbohydrates, called saccharolytic fermentation, occurs mainly in the proximal colon and produces short-chain fatty acids (SCFA), of which acetate, propionate and butyrate are the most common.(4, 5) These SCFA, which are the main fuel for colonocytes, are absorbed quickly, leading to an almost absolute absence of SCFA in the transverse colon. In absence of indigestible carbohydrates, the microbiome shifts to proteolytic fermentation in the transverse and distal colon, producing numerous substrates, such as indoles, tryptophane, ammonia and hydrogen sulphide.(3, 7-9)

In general, SCFA have a beneficial effect on human health. They improve gut health by improving epithelial function, intestinal barrier function and mucosal quality, and reducing gut permeability. SCFA also have a positive impact on metabolic health by reducing body weight, increasing energy expenditure, satiety, insulin sensitivity and adipose tissue lipid buffering capacity, and preventing low-grade inflammation and ectopic lipid accumulation. Furthermore, evidence shows that an increase in circulating SCFA reduces inflammation in the gut, pancreas and throughout the body, including the brain, by reducing cytotoxic T cell activity and increasing anti-inflammatory regulatory T-cells. Lastly, SCFA are found to reduce stress in rodents, as a

result of SCFA-induced reduced release of corticotropin-releasing hormone and downregulation of mineralocorticoid receptor expression.(3-6, 8-19)

Proteolytic fermentation, more prevalent in the transverse and distal colon, produces substrates, such as branched-chain fatty acids, ammonia and phenols, that can have detrimental health effects.(5, 20, 21) On the other hand, there are also indications that substrates of proteolytic digestion may have positive health effects. Proteolytic digestion, and especially digestion of tryptophan rich proteins, in the small intestine is associated with reduced inflammation and improved gut barrier function and increased satiety and weight loss/maintenance.(3, 22-27) Overall, the balance between saccharolytic and proteolytic fermentation products in different parts of the gut may be an important determinant of metabolic health.

Our recent studies have shown that delivering SCFA, acetate in particular, specifically to the distal colon yields beneficial health effects, such as increased fat oxidation, reduced lipolysis, increased satiety hormone concentrations and reduced inflammatory cytokines (TNF- $\alpha$ ). (28, 29) Apart from this, other studies have shown that delivering SCFA directly to the distal colon improves human metabolism and increases levels of satiety hormones and energy expenditure, which may be partly due to SCFA bypassing the liver and increasing peripheral SCFA concentrations.(28, 29) These effects were not present when acetate was administered to the proximal colon. We therefore hypothesize that an increased delivery of indigestible carbohydrates throughout the entire colon may have the most pronounced health effects by increasing distal saccharolytic fermentation and SCFA production, and thereby inhibiting proteolytic fermentation.

Increasing the SCFA concentration in the distal colon can be achieved by using complex carbohydrates, such as resistant starches or dietary fibres. These complex, indigestible carbohydrates escape fermentation in the small intestine, since the composition of the small intestinal microbiome differs from the colonic microbiome, lacking specific bacteria that are capable of fermenting these carbohydrates.(3-6, 8-10)

Many previous studies regarding manipulation of intestinal digestion and fermentation are performed on rodents, while evidence in humans is lacking. The few available human trials mainly describe acute interventions and present inconsistent data. Furthermore, the beneficial effects of SCFA on glucose homeostasis and insulin sensitivity are mainly found in lean individuals, and not in obese/(pre)diabetic adults.(28, 30-32)

The few human trials on long term effects of introduction of SCFA in the colon are mostly conducted in healthy adults, and results were not consistent. (33-35) This may be related to interindividual variation in response. We hypothesize that this is partly due to a different composition of initial microbiome, as well as differences in metabolic phenotypes (i.e. being insulin resistant or having prediabetes).

To this end, the aim of the present project is to determine the long-term effects (12 weeks) of an optimal balance between saccharolytic and proteolytic fermentation products on gut health, human metabolism and psychological state in humans with insulin resistance and/or prediabetes, and overweight. The present study might give rise to new possible preventative and therapeutic measures to reduce obesity and its related metabolic disorders, including insulin resistance, metabolic syndrome, type 2 diabetes mellitus and non-alcoholic fatty liver disease. Additionally, we expect that improving microbial composition and functionality may also improve brain health by supporting cognitive functioning and appetite regulation, altering reactions to food cues and reducing experienced stress.

## 2. OBJECTIVES

### *Primary Objective:*

The main goal of this study is to provide evidence that steering saccharolytic/proteolytic fermentation by a specific indigestible fibre mixture supplemented against the background of a high-protein diet optimizes beneficial and minimizes detrimental substrate production. Most importantly, we will be looking into changes in peripheral insulin sensitivity.

### *Secondary Objectives:*

Apart from determining possible effects on insulin sensitivity, we will also investigate the following parameters and analyse whether steering fermentation can influence the following secondary outcomes:

1. Hepatic and adipose tissue insulin sensitivity
2. Energy and substrate metabolism (energy harvest, energy intake, energy expenditure, fat and carbohydrate oxidation).
3. Circulating metabolites, inflammatory factors and blood lipid spectrum
4. Gut permeability
5. Brain health (neurocognitive functioning and food reward-related brain activity)
6. Adipose tissue and skeletal muscle metabolism
7. Composition and functionality of microbiome
8. Gastro-intestinal side-effects of provided dietary supplement against the background of a high-protein diet

Additionally, we will explore possible correlations in the gathered data, including anthropometric measurements, physical activity, dietary intake, glucose sensitivity, composition of gut microbiota, etc.

### 3. STUDY DESIGN

The proposed study will be a double-blind, randomized placebo-controlled trial, to evaluate the effect of a potato-pectin fibre mixture on gut, metabolic, immune and brain health by optimizing saccharolytic and proteolytic fermentation. Individuals aged 30-75 years with overweight or obesity ( $\text{BMI} \geq 28 \text{ kg/m}^2 < 40 \text{ kg/m}^2$ ) and impaired fasting glucose (defined as fasting glucose 5.6-6.9 mmol/l or HbA1c 42-47 mmol/mol) or insulin resistance ( $\text{HOMA-IR} > 1.85$ ) will be included in the study.

All visits regarding this study will take place at the facilities of the department of human biology or the Metabolism Research Unit Maastricht of Maastricht University, or at the clinical facilities of Maastricht University Medical Center+.

After the application of an individual via (e-)mail or phone (see [Chapter 4](#) for recruitment), the researcher will contact the potential participant by email or phone to provide additional information regarding the study, answer questions and determine possible eligibility, after which a week of consideration will be given. After a week, the potential participant will be contacted again and, if they are still interested in participating, a screening visit will be planned.

The first visit to our facilities will consist of the following components:

- Checking an individual's wellbeing, medical history and determining eligibility and safety of participation.
- Signing informed consent
- Measuring vital parameters and body measurements (body weight, length, waist-to-hip ratio, systolic and diastolic blood pressure)
- Taking blood samples to determine eligibility based on specific inclusion criteria (20ml to determine glucose, insulin, ALAT, creatinine, HbA1c)

The participant will visit our facilities after a >10h overnight fasted state.

All eligible participants will be equally randomized over the two arms (potato-pectin fibre mixture vs placebo) with stratification for age, sex and HbA1c (see [Chapter 8.2](#)). The entire trial period after screening and randomization will take 13 weeks, which will be explained in more detail below.

#### Intervention period

This randomized clinical trial with the primary outcome tissue-specific insulin sensitivity has a placebo-controlled, double blind, randomized parallel design, which allows evaluation of the role of a fibre mixture against the background of a high protein diet on host metabolism in male and female adult volunteers with overweight/obesity and impaired glucose homeostasis.

The approach is as follows:

1. Preceding this human intervention trial, a pilot study already has been performed to screen for the most optimal fibre mixture increasing distal colonic saccharolytic fermentation (and thus SCFA production) and inhibiting proteolytic fermentation. Faeces have been collected in 13 human volunteers with insulin resistance and overweight. The pooled faecal microbiota has been inoculated in TIM-2 to analyse SCFA and BCFA production after addition of different fibres or fiber combinations in a 24-h protocol against the background of a high-plant based protein mixture (which was comparable to the protein ratio as proposed in the human trial). The fibre mixture that resulted in the highest microbial SCFA production in the part of TIM-2 that represented the distal colon *in vitro* will be supplemented in the *in vivo* study. The hereby defined fibre mixture is composed out of potato and pectin fibres.
2. After randomization, the 12-week impact of a potato-pectin fibre mixture on tissue-specific insulin sensitivity will be determined in a randomized, double blind, parallel designed study.

Before the start of the intervention, participants will visit our facilities for the first clinical investigation days (CID 1 and 2). These days consist of the following test: (see [Chapter 8.3 Study procedures](#) for detailed description of the tests)

- Providing stool samples by participant
- Taking skeletal muscle and adipose tissue biopsies
- Performing two-step hyperinsulinemic-euglycemic clamp
- Performing indirect calorimetry during the clamp
- Performing gut permeability tests by intake of specific sugars dissolved in water and analysis of urine samples
- Conducting Functional Magnetic Resonance Imaging to study food-reward-related brain activity
- Conducting a DEXA scan to determine body composition
- Filling in questionnaires and performing neuropsychological tests
- Food diaries will be filled in prior to CID 1.
- Distributing and explaining of assigned intervention (a potato-pectin fibre mixture or placebo)

After CID 1, participants will be provided with a standardized meal. This meal needs to be consumed at home on the evening before CID 2 *ad libitum*. Afterwards, they should remain

fasted until the hyperinsulinemic-euglycemic clamp on CID 2. CID 2 will take place at least 2 days and preferably within 2 weeks after CID 1. In total, participants will visit the university after an overnight fast in week 6 and on all four CIDs.

After the 12 weeks of intervention, two additional CIDs (CID 3+4) will take place, which are similar to CID 1+2, respectively.

After completing the screening and CID 1+2, the intervention will consist of either a dietary supplement or a placebo which will have to be taken thrice daily during 12 consecutive weeks. Furthermore, all participants will receive a background diet high in protein 25EN% protein mixture, 30EN% fat, and 45EN% carbohydrates. Protein content will consist for 45-50% out of plant-based protein and for 50-55% out of animal-based proteins. The protein-rich products will be consumed during breakfast and dinner. The fibre mixtures and control product can be easily consumed with protein-rich food. The exact diet composition will be discussed individually to establish a diet suited to the participants' needs and taste. The energy requirements for this diet will be estimated using indirect calorimetry based on resting energy expenditure and an activity factor of 1.5.

Both the participants and investigators will be blinded to the treatment. The study is designed to study the dietary fibre effects against the background of a high protein diet independent of any diet or exercise intervention.

In week 2, 6 and 9, participants will return for a short interview or will be contacted via telephone to assess their wellbeing and compliance, answer arisen questions and fill in questionnaires. Additionally, a stool and blood sample will be provided in 6. Questionnaires will mainly be filled in before and after the intervention, with the addition of SQUASH and three-day food diary in week 6, and BSS and GSRS in weeks 2, 6 and 9.

To screen their food intake and physical activity (SQUASH), participants will fill in a three-day food diary before each CID 1+3 and on week 6. Gastrointestinal Symptom Rating Scale (GSRS) questionnaire will be completed the day before the CID1+3 and on weeks 2, 6 and 9. Therefore, we can screen whether the participant might experience gastrointestinal discomforts during the intervention period such as bloating and the outcomes are also relevant for our faecal microbiota analysis.

After completion of the trial, all data will be gathered and analyzed. Participants will receive a financial compensation for their efforts, as well as reimbursements of their travel expenses.

The total amount of time participants spend at our facilities will be around 36 hours (Screening: 1h; CID 1+2: 7+9.5h; Interview week 2, 6, 9: 3 x 0.5h; CID 3+4: 7+9.5h).

As mentioned before, CID 3 will be planned 12 weeks after the start of the intervention. The dietary supplement/placebo and the protein-rich diet will have to be continued until CID 3, which means that in some cases the intervention period will be not exactly 12 weeks, but a few days longer or shorter, depending on the availability of the participant. Logically, the investigators aim for CID 3 to be planned exactly 12 weeks after the start of the intervention. The reason the intervention needs to be continued until the day before CID 3, is to ensure possible acute effects of the intervention on the experiments/outcomes are comparable between participants. It is hypothesized that the small differences in total length of the intervention will not substantially interfere with the outcome measures.

The researchers aim to adhere to the proposed schedule of the test days. However, if necessary, test day schedules might have to be altered due to logistical reasons.

[figure not shown]

Figure 1. Study design

Tables 1 and 2. Clinical investigation day 1 and 2

| Clinical investigation day 1 |                                              |
|------------------------------|----------------------------------------------|
| 08.00u                       | Measuring anthropometrics                    |
| 08.15u                       | Multisugar test → start 24h urine collection |
| 08.45u                       | fMRI                                         |
| 10.00u                       | Subcutaneous adipose tissue biopsy           |
| 10.45u                       | Questionnaires + CANTAB                      |
| 12.15u                       | DEXA-scan                                    |
| 13.15u                       | Collect 5h urine                             |

| Clinical investigation day 2 |                                                                                                |
|------------------------------|------------------------------------------------------------------------------------------------|
| 08.00u                       | Arrival after >10h fasting after standardized meal.
Providing of 24h-urine + faecal samples |
| 08.15u                       | Insertion cannulas, blood sampling                                                             |
| 08.30u                       | Start clamp                                                                                    |
| 09.00u                       | Skeletal muscle tissue biopsy                                                                  |
| 10.00u                       | First indirect calorimetry                                                                     |
| 13.00u                       | Second indirect calorimetry                                                                    |
| 15.30u                       | Third indirect calorimetry                                                                     |
| 16.30u                       | End clamp                                                                                      |

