### **8.3 Study procedures**

Whenever participants are expected to be physically present at our facilities, they will be asked to travel by car or public transport to limit the physical activity prior to the experiments.

Prior to the screening and CIDs, subjects are asked to refrain from alcohol and strenuous physical activity 24h and need to arrive in the morning after a >10h overnight fasting period.

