### 8.3.9 Tissue biopsies

On CID 1 and 3, after the DEXA scan, tissue biopsies will be taken from abdominal subcutaneous adipose tissue (scAT) and skeletal muscle tissue (SMT). In both tissues, the expression of genes, proteins and pathways related to adipogenesis, lipid metabolism oxidative metabolism and inflammatory profile will be analysed by standard PCR and blotting methodologies. Biopsies will be taken in >10h fasting state.

*Adipose tissue biopsy*

An abdominal subcutaneous adipose tissue biopsy will be performed using needle biopsy to obtain approximately 1 gram of adipose tissue. After administering of local anesthesia (lidocaine 2%), a needle biopsy will be performed.

*Muscle tissue biopsy*

A skeletal muscle biopsy will be taken from the *m. vastus lateralis*. After locally administered anesthesia (lidocaine 2%), the skin and fascia will be opened using a small incision. Afterwards, the biopsy needle will be inserted into the muscle to obtain several muscle samples using suction. A total of approximately 100mg will be collected. After the biopsy, the site of insertion will be closed using a Steristrip® and bandaged with Tegaderm® and Acrylastic® pressure bandage.

Besides changes in SCFA receptor GPR41/43 expression in these tissues, signalling pathways involved in insulin signalling and oxidative metabolism (i.e. phosphorylation of IRS1, PKC and AMPK, as well as PGC-1 $\alpha$  and PPAR $\alpha/\gamma$ ), lipolysis (i.e. total and phosphorylated HSL, ATGL and its co-activator CGI-58 and PLIN1), and inflammation (i.e. NF $\kappa$ B, CD68, Interferon- $\gamma$  and MCP) will be analysed in these samples using RT-qPCR and/or Western Blot. In this project we will focus on adipose tissue and skeletal muscle metabolism, since alterations in adipose tissue and muscle functionality could play a key role in the SCFA induced improved peripheral insulin sensitivity, by affecting lipolysis and proinflammatory processes in adipose tissue and fat oxidation in skeletal muscle. Additionally, adipocyte size will be determined. If budget allows, untargeted gene sequencing will be performed.

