**8.3.10 Two-step hyperinsulinemic-euglycemic clamp**

To assess whole-body and tissue-specific insulin sensitivity, we will be performing a two-step hyperinsulinemic-euglycemic clamp, which is the gold standard to determine insulin sensitivity. The clamp will be performed on CID 2 and 4 and will take place after a >12h overnight fasting period and a standardized meal the evening before. Before starting the procedure, an intravenous canula will be inserted in an antecubital vein to provide intravenous access for insulin and glucose suppletion. Another intravenous canula will be inserted on the dorsal side of the contralateral hand to ensure intravenous access for blood sampling.

At  $t = 0$  minutes, a fasting blood sample (10ml) will be drawn, followed by infusion of a primed 6,6-H2-glucose tracer at 0.04mg/kg/min, which will be used to calculate endogenous glucose production (EGP), glucose appearance (Ra) and glucose disposal. Therefore, blood samples (6ml) will be drawn at  $t=90$ , 105 and 120 min. At  $t = 120$ min, insulin will be infused at a low,

constant rate of 10 mU/m^2/min for 3 hours to allow determination of hepatic glucose production. After 3 hours ( $t = 300\text{min}$ ), insulin infusion will be increased to 40 mU/m^2/min to inhibit EGP for 2.5 hours, providing insight in muscle insulin sensitivity. During insulin suppletion, plasma glucose levels will be measured every 5 minutes (1ml), upon which glucose (20% glucose solution) will be infused at 10-30ml/h to ensure a constant plasma glucose level of 4.8-5.2 mmol/l during the clamp. Afterwards, the total amount of infused glucose can be used to determine insulin sensitivity. Additional blood samples (6ml) will be drawn at  $t = 180, 240, 270, 285, 400, 420, 435$  and 450 minutes.

At  $t = 450\text{min}$ , insulin infusion will be terminated and glucose infusion will be slowly reduced to zero to ensure a safe normalisation of glucose homeostasis. Additional dietary supplements will be provided (sandwiches, drinks) to prevent a hypoglycemic state.

During the clamp, an indirect calorimetry will be performed, which will be described below.

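### The meal before the primary-endpoint clamp is called standardised but is eaten in free amounts, and the minimum fast is stated two ways, so pre-clamp conditions can vary between visits and participants

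*Protocol*

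**What the plan says.** **Meal.** Protocol section 3 (Intervention period) states: "After CID 1, participants will be provided with a standardized meal". The next sentence adds: "This meal needs to be consumed at home on the evening before CID 2 *ad libitum". Participants then stay fasted until the clamp. For the end of the study, section 3 says only that "two additional CIDs (CID 3+4) will take place, which are similar to CID 1+2, respectively". Section 8.3.10 applies the meal to both clamps, which "will take place after a >12h overnight fasting period and a standardized meal the evening before".

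**Fast.** The CID 2 timetable in section 3 reads "Arrival after >10h fasting after standardized meal", with arrival at 08.00. Section 8.3 says that before screening and every CID participants "need to arrive in the morning after a >10h overnight fasting period". Section 8.3.10 requires more than 12 h for the clamp. Section 8.3.9 adds "Biopsies will be taken in >10h fasting state", and the timetable places the muscle biopsy at 09.00 on the clamp day.

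**Intake records.** The three-day food records belong to the periods before CID 1 and CID 3 and to week 6 (sections 3, 8.1.3 and 8.3.12).

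**The concern.** A standardised meal before a clamp serves its purpose if participants start the two measurements in a similar state. With free intake, only the composition of the meal is held constant. Energy and carbohydrate eaten can differ between people and, more importantly for a pre-to-post comparison, within a person between CID 2 and CID 4. Nothing in the protocol would reveal such a difference afterwards.

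The two fasting minimums add to this. Staff who check arrivals against the timetable would accept visits that the clamp section does not allow. A participant between the two limits could be called compliant or deviating, which matters because section 10.1 plans a per-protocol analysis.

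At stake is precision. The endpoint in section 8.1.1 is a difference in change, and the sample size in section 4.4 rests on a pre-post correlation of 0.73, so comparable conditions at the two clamps are worth protecting. Section 3 accepts this reasoning elsewhere: it continues the intervention to the day before CID 3 so that acute effects are comparable between participants.

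**Working it through.** **Step 1. Meal provisions side by side.**

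| Feature | Before CID 2 | Before CID 4 |
|---|---|---|
| Meal supplied | Yes, called standardised (section 3) | Yes, through section 8.3.10 and the similarity clause in section 3 |
| Amount | Free | Not stated separately |
| Clock time | Evening only | Evening only |
| Amount or time recorded | No | No |
| Matched to the other clamp | No | No |

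CID 2 falls at least 2 days after CID 1, so a food record kept before CID 1 cannot include the evening before CID 2. If CID 4 follows CID 3 with the same spacing, as the similarity clause implies, the record kept before CID 3 misses the evening before CID 4 in the same way.

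**Step 2. Latest permitted meal under each fasting rule.** Inputs: arrival 08.00 and clamp start 08.30 (CID 2 timetable).

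- More than 10 h at arrival: 08.00 − 10 h, so last intake before 22.00.
- More than 12 h counted to arrival: 08.00 − 12 h, so before 20.00.
- More than 12 h counted to clamp start: 08.30 − 12 h, so before 20.30.
- Gap: 22.00 − 20.30 = 1.5 h, up to 22.00 − 20.00 = 2 h.

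A participant who finishes at 21.00 has fasted 11 h at 08.00 and 11.5 h at 08.30. That satisfies the timetable and section 8.3 but breaches section 8.3.10 on either count.

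**Step 3. Can the rules be read as agreeing?** Section 8.3.10 starts insulin at t = 120 min. With t = 0 at 08.30, that is 10.30. This fits the timetable, where the first calorimetry (t = 90 min) is at 10.00. A participant meeting only the 10 h rule has fasted more than 12.5 h at 10.30, because 22.00 to 10.30 is 12.5 h. The rules would agree only if the 12 h were counted to insulin start. Section 8.3.10 does not say so, and it states the fast before it describes cannula insertion.

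**Step 4. What extra noise would do (illustration only).** The documents give no figure for the effect of meal or fast on the clamp result. Section 4.4 gives SD 3.95, r = 0.73, residual SD √(1 − 0.73²) × 3.95 = 2.70, and a target difference of 2.86 µmol/kg/min. After 20% dropout, 22 × 0.80 = 17.6, taken as 17 per arm.

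Assume that uncontrolled conditions add a fraction f of 3.95² to the variance at each visit, beyond what the planning data already contain. Then r′ = 0.73/(1 + f), and residual SD′ = 3.95 × √(1 + f) × √(1 − r′²). Power is for a two-sided two-sample t-test at 5%.

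| Assumed f | r′ | Residual SD′ | Power, 17 per arm |
|---|---|---|---|
| 0 | 0.73 | 2.70 | 85% |
| 0.05 | 0.70 | 2.91 | 79% |
| 0.10 | 0.66 | 3.10 | 74% |
| 0.20 | 0.61 | 3.43 | 65% |

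The first row, no extra noise, is as compatible with the documents as the others.

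**The case against.** Several points on the other side are sound.

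- **A standardised meal can mean fixed composition with free quantity.** That reading removes the verbal contradiction. It leaves the amount and time unmatched across the two clamps.
- **The two fasts are minimums, and a fast longer than 12 h meets both.** The muscle insulin sensitivity step starts at t = 300 min, or 13.30, when even a participant meeting only the 10 h rule has fasted more than 15.5 h from food, with glucose infused in between. The conflict is therefore modest for the endpoint, but it still needs one answer.
- **Standard operating procedures exist for each measurement (sections 11.4 and 13.1) and are not shown.** They may fix portion and timing. They could not agree with both fasting rules as written.
- **The 0.73 comes from the group's earlier clamp trials (section 4.4).** If those used similar meals, this noise is already in the figure. It cannot be said that the correlation will be lower than planned.

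A reader might infer a bias between arms: the introduction credits short-chain fatty acids with "increasing energy expenditure, satiety, insulin sensitivity and adipose tissue lipid buffering capacity" and later expects better appetite regulation, so the fibre group might eat less before CID 4. The documents do not support that step. Supplement and diet end the day before CID 3 (sections 3 and 5.1). If CID 4 comes at least 2 days after CID 3, its evening meal falls at least 2 days after the last supplement day. An arm difference would need an appetite effect that outlasts the supplement, and none is shown. The fasting rules are the same in both blinded arms.

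**Conclusion.** The point holds as a matter of measurement standardisation. The protocol leaves the amount and timing of the pre-clamp meal open and unrecorded at both primary-endpoint clamps, and it gives two minimum fasts for the same visit that differ by 1.5 to 2 h in the latest permitted meal. This permits avoidable variation in pre-clamp state between visits and between participants.

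The size of the effect on the endpoint is unknown. The power figures above show the direction and sensitivity under assumed noise and are not an estimate. In expectation the variation is alike in both arms; a between-arm difference through appetite is possible only with carry-over after the supplement stops. The conclusion rests on the protocol text alone and assumes that CID 4 mirrors CID 2, as section 3 indicates. It should be corrected, but it does not undermine the design.

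**What to change.** In section 3, replace free intake with a defined amount of the meal already supplied. Record the amount eaten and the clock time on the evening before CID 2, and repeat the same amount and time before CID 4. State the CID 4 requirement explicitly instead of leaving it to the similarity clause. The amount should not depend on the calorimetry-based energy requirement, because sections 8.3.11 and 3 place that measurement during the CID 2 clamp, after the first meal has been eaten.

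Reconcile section 3 (text and CID 2 timetable), section 8.3 and section 8.3.10 to one minimum fast. Name the time point to which it is counted, such as arrival, clamp start or insulin start, and apply it at both clamps. Which minimum applies is for the sponsor to decide. Section 8.3.9 should then be checked against it for the clamp-day biopsy.

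The cost is wording in a few sections, portioning of a meal the site already provides, a brief intake record at two visits, and slightly less freedom for participants on those evenings.
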